## 8. Co-administration MDA Strategy

### 8.1. Statistical Methods

Clinical Randomized Controlled trials often try to demonstrate that one form of treatment is better than an existing treatment, typically known as a superiority trial. However, within this co-administration study, the goal is not to demonstrate the superiority of triple-drug administration over standard MDA in terms of efficaciousness. Rather, the study is will demonstrate whether administering all three drugs together is no worse, within a specified margin, than giving all three drugs via the standard distribution format. The possible benefit of the co-administration trial will most likely lie in improved convenience and cost without any increase in negative outcomes, not necessarily in improved treatment results. For that reason, the study will use a non-inferiority trial model.

Within our standard arm, the study will deduce the average adverse event rate for azithromycin administered alone using information from previous trials, and it will assume an average adverse event rate for azithromycin, ivermectin and albendazole administered together. For azithromycin, there is a wide-range of reported adverse event rates. The aforementioned co-administration trial in Mali assumed an adverse event rate of 8%. A randomized control trial using a single dose of azithromycin which took place in the United States reported adverse events at 17%. A randomized control trial in Ethiopia reported that monitored adverse event rates after Zithromax MDA reported 4.9%-7.0% adverse events in children from 1-9 years old and 17.0% to 18.7% in persons  $\geq 10$  years of age. Meanwhile, Pfizer labeling reports the following: "Side effects that occurred in patients on the single one-gram dosing regimen of Zithromax with a frequency of 1% or greater included diarrhea/loose stools (7%), nausea (5%), abdominal pain (5%), vomiting (2%), dyspepsia (1%) and vaginitis (1%)." For the purposes of this study, we will set the adverse event percentage at 7% for azithromycin distribution. In terms of the adverse even rate during co-administration of all three drugs, adverse events related to IVM and ALB distribution are largely due to the death of microfilariae, particularly after the first round of MDA in a community. Given that this community has received several years of treatment with both drugs, we assume an acceptable increase in adverse events during co-administration will be 1.5% (Delta), or it will be acceptable for 8.5% of our intervention arm to experience an adverse event.

The study will require a power of 90% and a two-sided 95% confidence interval for the difference between rates. Given that gotes will be randomly selected from within the same woreda, have all had the same number of years of treatment with each drug, and share the same cultural and environmental factors, we will assume a low variability between each cluster. In case there are unforeseen differences between the clusters, we will include a variance between 6-8%. Conservatively assuming that each gote has a population of 190 individuals, the study will require at least 36 gotes in each study arm to reach 13,600. To take non-compliance, etc. into account, the study will randomize the 42 gotes into each study arm to reach 8,000 participants in each arm from the list of gotes in Kofele woreda into the control and study arms until each arm has 8,000 participants (to account for non-compliance, etc.). Gotes will be chosen via the RANDNUM function in excel. The randomization itself will be conducted via public randomization ceremonies.

Table 2: Assumption Summary

|                                                               |                                                           |
|---------------------------------------------------------------|-----------------------------------------------------------|
| Adverse event prevalence                                      | 7% on average                                             |
| Acceptable adverse event percentage during co-administration: | 8.5%                                                      |
| Delta                                                         | 1.5%                                                      |
| Variance                                                      | Adverse event prevalence between clusters will be 6-8%    |
| Power                                                         | 90%                                                       |
| CI                                                            | 95%                                                       |
| Minimal Number of Gotes Required for each arm                 | 36                                                        |
| Population per cluster                                        | 190 individuals per cluster (gote) on average             |
| Total Population of Study                                     | 13,600 (Rounded to 16,000 for refusals/loss to follow up) |

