| Title              | Safety of the co-administration of azithromycin, albendazole and ivermectin versus standard treatment regimens during mass drug administration (MDA) in Ethiopia: a cluster-randomized trial                                                                                                                                                                                                                                                                                                                                                                                                                                                                                                                                                                                                                 |
| Objective          | To establish the safety profile, assess the community acceptance, and weigh the economic advantages of a three-agent MDA combining azithromycin, albendazole (Alb), and ivermectin (Ivm) in comparison to the standard MDA regimen which separates the administration of azithromycin from the dually administered ivermectin and albendazole by a period of two weeks.                                                                                                                                                                                                                                                                                                                                                                                                                                      |
| Design             | A cluster-randomized non-inferiority trial to assess the safety, local acceptance, and economic advantages of combined MDA with azithromycin, albendazole, and ivermectin in one district in Oromia, Ethiopia. Within this district, a study group of 8,000 people will receive the triple drug co-administration. A control group of 8,000 people within the same district will receive the standard MDA treatment beginning with Ivm/Alb followed two weeks later with azithromycin. The study will randomly sort sub-district communities ( Gotes ) into the trial arm and the control arm. The study will compare the “baseline” of adverse events (AEs) and severe adverse events (SAEs) between the two arms to determine if the triple drug therapy is not inferior to the standard treatment. |

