### 1.8. Past studies involving permutations of azithromycin, IVM and ALB combined

**Mali:** This was a study in four randomly assigned villages (N=3, 011) endemic for trachoma and LF. Two villages were randomized for “co-administering ivermectin, albendazole, and azithromycin” and two villages were given the standard treatment of one round of OV/LF MDA followed one week later by a round of azithromycin MDA. In the study, the overall reported rates of any adverse event were similar: 18.7% (281/1501) in the co-administration arm and 15.8% (239/1510) in the standard treatment arm. No serious adverse event was reported. However, the study was too small to justify a definitive recommendation.

**Solomon Islands:** a field trial of co-administration of azithromycin and ivermectin mass drug administration for scabies and trachoma (N=26,188) revealed no safety issues with combining azithromycin and ivermectin. Follow up was completed for 21,931 participants (83.7%) and identified no serious adverse events. Adverse events were noted in 2.6% of participants across the entire study population; the most commonly reported adverse events were dizziness, abdominal pain and diarrhoea. This study did not, however, include the addition of albendazole.

**Colombia:** At the programmatic level, this work involved reaching remote trachoma and STH co-endemic populations. More than 305,005 people received albendazole and azithromycin together for three separate annual cycles (2012-14). The reported adverse events were headaches, dizziness and diarrhoea in 0.16% of those surveyed (7 out of 4,438 people). No serious adverse events were documented. However, the findings are not statistically powered.

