**On Day 17, 18**, the clinical nurses and HEW from each of the original four teams will perform one last house to house follow up of all the households that received the triple drug administration. (400 HH x 4 teams = 1600 HH) This will be the last active follow-up step.

**Day 19-30**, the HEWs will maintain the reporting form for another two weeks in the event of any additional complaints from the targeted beneficiaries. This will be completely passive and the HEW will only log complaints if they are reported by a beneficiary. On Day 30, all of the co-administration registers and forms will be collected for data analysis from the HEWs.

Note that in the “standard MDA” control arm, the process described above will be conducted twice. First, IVM/ALB MDA will take place for with 14 days of active surveillance then the Trachoma MDA will take place for 14 days of active surveillance. Passive surveillance will continue in the control arm for two weeks after that.

Once the 45th day of the study is reached in Oromia, the field implementation portion of the study will be complete. The DSMB will review the final data before making a recommendation on how the remainder of the population in the woreda should be treated. Should the DSMB and the FMOH agree, the remaining 4-5000 beneficiaries within Homesha will be targeted for co-administration. However, at this juncture, the RCT will be over. The study will move to strictly observational with the same enhanced supervision in place.

Table 3: Follow up Schedule for both the Trial and the Control Arms of the Study

|                                                    | Day 1 | Day 2 | Day 3 | Day 4 | Day 5 | Day 6 | Day 7 | Day 8 | Day 9 | Day 10 | Day 11 | Day 12 | Day 13 | Day 14 | Day 15 | Day 16 | Day 17 | Day 18 | Day 19-30 | Day 31 |
|----------------------------------------------------|-------|-------|-------|-------|-------|-------|-------|-------|-------|--------|--------|--------|--------|--------|--------|--------|--------|--------|-----------|--------|
| Actual Distribution                                |       |       |       |       |       |       |       |       |       |        |        |        |        |        |        |        |        |        |           |        |

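### The 90% power rests on a 7% adverse event rate for azithromycin alone, although the control arm receives all three drugs; at the higher rates the protocol itself cites, the same sample size gives clearly less

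*Protocol*

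**What the plan says.** Section 8.1 names the source of the control rate: "Within our standard arm, the study will deduce the average adverse event rate for azithromycin administered alone using information from previous trials". After listing a wide spread of published figures it settles the value: "For the purposes of this study, we will set the adverse event percentage at 7% for azithromycin distribution". The margin is 1.5 percentage points, so up to 8.5% is acceptable under co-administration. On precision it says: "The study will require a power of 90% and a two-sided 95% confidence interval for the difference between rates". Table 2 lists 7% as the AE prevalence without saying which regimen it belongs to, together with 6-8% between clusters, 190 people per gote and at least 36 gotes per arm.

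The control arm, according to the Study Protocol Summary, "will receive the standard MDA treatment beginning with Ivm/Alb followed two weeks later with azithromycin". Section 8.8 adds: "Note that in the “standard MDA” control arm, the process described above will be conducted twice". AEs are therefore collected after each of the two rounds.

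Two cited sources bear on the rate. Section 1.8 reports, for the Mali trial of the same comparison, "18.7% (281/1501) in the co-administration arm and 15.8% (239/1510) in the standard treatment arm". Section 8.1 cites, for azithromycin MDA in Ethiopia, 4.9-7.0% at ages 1-9 and "17.0% to 18.7% in persons" aged 10 and over. Section 7.2 excludes children under five.

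**The concern.** The planning rate belongs to a treatment that neither arm receives. It is also the upper end of a range for children aged 1-9, applied to a population aged five and over.

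With a fixed absolute margin this matters, because the binomial variance p(1-p) grows with p over this range. A higher control rate widens the confidence interval for the difference, while the 1.5-point margin stays where it is. If the true rate lies well above 7%, the stated 90% overstates the chance of showing non-inferiority when the two regimens are in fact equal. A reader of the result would then misjudge what an upper limit beyond 1.5 points means.

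**Working it through.** **Inputs.** Margin 0.015, one-sided 2.5% (two-sided 95% interval), 90% power, m = 190 per gote and 36 or 42 gotes per arm (Section 8.1, Table 2); evaluable target 6,840 per arm and a 15% cushion (Section 6). The document does not say what 6-8% between clusters means. I read it as 7% plus or minus 2 SD, so SD = 0.005 (assumption). The true difference is taken as zero.

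**Reproducing the plan.** The usual cluster formula for two proportions is

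c = 1 + (1.960 + 1.282)² × [2p(1-p)/m + 2·SD²] / 0.015².

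At p = 0.07: 2(0.07)(0.93)/190 = 0.000685 and 2(0.005)² = 0.000050. Then c = 1 + 10.51 × 0.000735/0.000225 = 35.3, hence 36 gotes and 36 × 190 = 6,840 per arm, as stated.

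Other readings, all at a 7% control rate:
- 6-8% as a uniform range: 36.1
- 6-8% as plus or minus 1 SD: 42.3
- no clustering: 33.0
- 8.5% in the co-administration arm's variance: 39.0 with the SD scaled to the rate, 36.1 with no clustering (which drops the stated allowance)

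**Power at other rates.** SE = √{[2p(1-p)/m + 2·SD²]/c} and power = Φ(0.015/SE - 1.96). The SD is either held at 0.005 or scaled with the rate (0.005/0.07 × p, which is 0.0113 at 15.8%). Ranges run from scaled to fixed SD.

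| Control rate | 36 × 190 = 6,840 per arm | 42 × 190 = 7,980 per arm, if all evaluable |
|---|---|---|
| 7% | 91% | 95% |
| 10% | 79-81% | 85-87% |
| 12% | 72-75% | 78-81% |
| 15.8% | 60-66% | 67-72% |

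Worked line at 15.8%, 36 gotes, fixed SD: SE = √[(0.001400 + 0.000050)/36] = 0.00635; 0.015/0.00635 - 1.96 = 0.40; power 66%. With the scaled SD, SE = 0.00678 and power is 60%.

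**Which column applies.** The six extra gotes are the allowance for non-compliance and exclusions. After 15% loss, 0.85 × 7,980 = 6,783, or about 161 per gote in 42 gotes. Power is then 91% at 7% and 61-66% at 15.8%, practically the first column. Section 8.8 likewise expects about 6,800 people per arm in 42 gotes.

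**Confidence interval half-width** (1.96 × SE, 36 × 190): 0.89 points at 7%; 1.24-1.33 points at 15.8%.

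**Rate implied by the Ethiopian source.** If 10-30% of participants are aged 5-9 (assumption), the cited rates mix to between 0.30 × 4.9 + 0.70 × 17.0 = 13.4% and 0.10 × 7.0 + 0.90 × 18.7 = 17.5%, for azithromycin alone.

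**The case against.** The calculation itself is sound: 36 gotes follow from 7%, and the protocol declares 7% openly as an assumption after showing how widely published rates vary. What is in dispute is the planning assumption, not the arithmetic. That stands.

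The 15.8% is weak evidence. It comes from two villages per arm with rounds one week apart rather than two, in a trial that Section 1.8 itself calls too small for a definitive recommendation. Whether its AE definition matches Section 8.4 cannot be checked. A reader might take 15.8% as the true control rate; the documents do not establish that, and it is used here as one scenario. The protocol also cites lower figures: 8% assumed in the Mali trial, 2.6% in the Solomon Islands and 0.16% in Colombia. The first is a planning value and the other two are two-drug programmes, so none replaces an observed rate for the sequential regimen.

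Section 8.1 argues that ivermectin/albendazole events stem largely from dying microfilariae and that this community has been treated for years. That could keep the added events few. But the argument is used to support delta, carries no number, and does not lower the azithromycin component.

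Section 8.9 softens the consequence: missing 1.5 points while staying below 5 may still favour co-administration. With a true difference of zero, power to exclude 5 points is practically 100% at every rate above. So a reader should not infer that a miss means a failed trial, or that it would probably reflect low power; the latter depends on the unknown true difference.

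Nor does the Mali difference (18.7 - 15.8 = 2.9 points) show a power defect. If such a difference were true, it would exceed the margin, and not declaring non-inferiority would be the correct result.

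**Conclusion.** The point holds as a defect of the planning assumption. The 90% and the 36 gotes depend on a 7% rate taken from azithromycin alone and applied to a control arm given three drugs in two monitored rounds, while the protocol's most relevant citations lie well above 7%. At the planned evaluable size, power falls from about 91% at 7% to 60-66% at 15.8%, and is already 79-81% at 10%. The 95% and 67-72% in the second column apply only if every person in all 42 gotes were evaluable, which the 15% cushion contradicts.

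These figures assume a true difference of zero, 190 people per gote, and 6-8% read as about plus or minus 2 SD or a similarly narrow range. Reading it as plus or minus 1 SD would lower power further, but does not give 36 gotes. The margin, the analysis and the decision rule are not affected.

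**What to change.** In Section 8.1 and Table 2:

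- Base the control rate on the standard three-drug regimen, label it so, and give the reason for the value chosen.
- Replace the single 90% with power at 7%, 10%, 12% and 15.8%, computed on evaluable numbers: about 91%, 79-81%, 72-75% and 60-66%, with the reading of 6-8% stated.
- State the expected half-width of the 95% interval, about 0.9 points at 7% and about 1.25-1.33 points at 15.8%, and refer to Section 8.9, so that an upper limit between 1.5 and 5 points is read correctly.
- Leave delta at 1.5 points.

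The cost is wording and a less favourable stated power. No participants are added.

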## 8.2. Awareness Creation, Community Mobilization Mechanism, and Training

The roll-out will begin with a joint TOT in Addis led by the FMOH, AHRI and LSHTM. Each study team will include medical and public health professionals experienced in clinical trials and NTD MDAs. The TOT will be an opportunity to review the training modules, assess the monitoring plan, and establish agreed upon courses of action for predictable eventualities.

Note that before the study begins, the FMOH and appropriate RHBs will work with the zonal and woreda-level offices where the study will take place to ensure full understanding and compliance with the study parameters. It is important to note that the communities in Kofele district will be excluded from the usual MDA training cascade which begins at the regional level and then descends down the zonal, woreda-level, and kebele-level tiers where Health Extension Worker (HEW) and Health Development Army (HDA) are the final training recipients. In place of this cascade, the FMOH/AHRI/LSHTM team will provide protocol specific training to the woreda health officers and the health extension workers. The training modules will include an overview of the national NTD training manual followed by an in-depth explanation of the study protocol and how it differs from the common MDA procedure. Training modules that will be modified from the usual NTD training will include:

- Given the possible pill burden of co-administration (up to nine pills for an adult), HEWs will be taught to allow beneficiaries a maximum swallowing regiment (two pills, swallow, two pills, swallow) in order to discourage rushed administration and any possibility of choking. HEWs will be taught to encourage patients to take one pill at a time if they prefer.
- The study team will train the HEWs and Woreda Health Officers on the protocol for reporting to the local medical team that will be stationed nearby during the study.
- The FMOH and the study team will create a mobilization plan with the HEWs that will rely on the Health Development Army and local leaders to create awareness of the study which in turn will help ensure participation. This will enable the project to get a collective informed consent for the activity by the community.

After getting the collective informed consent of the community, the HEWs will update the MDA register with the population and household information within the community as per the usual pre-MDA registration activities. While going house to house, the HEWs will read the study consent form to all members of the household and gain their verbal permission to participate in

the study. For those participants that refuse consent, they will be allowed to receive MDA treatment via the usual MDA schedule of IVM/ALB dose followed by azithromycin dose two weeks later.

### 8.3 Co-Administration Team Allocation

Once the training and social mobilization is complete, the directly observed MDA by co-administration of azithromycin, ivermectin and albendazole will be conducted through the regular channels of distribution via the community health structure. Within each of the two study arms, four teams will operate simultaneously within four separate gores. At the actual distribution site, each team will address 300 people (roughly 60 households) per day. Assuming six hours (360 minutes) are allotted to each day for this co-administration exercise, each beneficiary would be allocated roughly 1.2 minutes to receive their treatment. In a normal MDA, this ratio would be easy to accommodate. However, given the need to complete the participant recruitment form (Appendix 2) for each beneficiary and to directly observe the administration of up to 9 pills (see the swallowing regimen referenced above), each team will form two, distinct distribution lines at the MDA site targeting 150 people each, resulting in a ratio of 2.4 minutes per beneficiary. The study will also only target 300 beneficiaries (60 HH) a day per team to facilitate the thorough follow-up of all 60 HHs the following day.

### 8.4 Recording of any AE/SAEs

The study defines AEs and SAEs per the national guidelines which are also found in the Serious Adverse Events handbook created by RTI ENVISION and the Task Force for Global Health:

**“Adverse event from MDA (AE-F-MDA)** is a medical event that takes place in an MDA program, causes concern in the medical and wider community and is believed to be caused by the drug(s) used. It can be caused by either administration of the drug or by a coincidental event that by chance happened after drug administration. Most AEs-f-MDA (adverse events from MDA) are self-limiting and treatable using simple remedies and are not usually required to be reported to national or international regulatory authorities.

**Serious Adverse Event (SAE)** is a regulatory term describing any untoward medical occurrence with any of the following characteristics:

- Results in death;
- Requires in-patient hospitalization;
- Results in persistent or significant disability;
- Is life-threatening; or
- Results in a congenital anomaly/birth defect.”

All adverse events will be recorded and followed up by the nurses on the team. The reporting of adverse events will be systematic and comply with national AE/SAE reporting guidelines to avoid any bias related to the wording of the question(s).

While the difference between “adverse events” and “serious adverse events” have been described above, there is also a level of severity which the study will also monitor: “The term “severe” is often used to describe the intensity (severity) of a medical event, as in the grading “mild”, “moderate”, and “severe”; thus a severe action need not be serious.” Reported adverse events will be classified according to their intensity (none, mild, moderate, and severe).

- Mild: easily tolerated, does not interfere with daily activity,

- Moderate: uncomfortable enough to interfere with daily activity,
- Severe: precludes daily activity (Given that a “severe” adverse event includes inability to complete daily activities, it will be classified as a possible SAE for the purposes of this study.)

The evolution of older complaints will be classified as: exacerbated, ongoing, and improved or resolved/none.

